### Interventions

2.6

Both groups undergo an 8‐week intervention program, consisting of three sessions per week, with each session lasting 45–60 min, following the designed treatment protocol.

The SDM group receives manual therapy based on the SDM approach for PHP. This technique targets the calf muscles using graded interventions classified by pressure velocity and biomechanical positioning, combined with stretching of myoneural structures [17]. The MFR group receives MFR therapy, involving deep stripping of the plantar fascia and targeted surface points of the calf muscles, following a standard protocol [18]. Both groups receive designed conventional physiotherapy treatment including ankle strengthening exercise, therapeutic ultrasound, and ice compressions [18, 19, 20, 21, 22]. Detailed descriptions of the interventions for both groups are provided in Table 2.

**Table 2 hsr272255-tbl-0002:** Intervention details.

Exercise	Description	Dosages
*Structural Diagnosis and Management Approach (SDM)*		
Calf muscle release [17]	Prone position: Superior to inferior; Lateral to medial Or, Supine position: Release with rolling techniques	10 repetitions for each direction/technique; 1–3 sets Application of gentle‐firm‐deep pressure
Calf muscle stretching in ankle dorsiflexion position [17]	Stretching of both the gastrocnemius and the soleus in different positions Application of one‐third to two‐thirds of the full dorsiflexion technique	10 repetitions; 15 s' hold; 1–3 sets
Myoneural stretching [17]	Hip and knee flexed to 90° Modified straight leg raise with ankle dorsiflexion	3–5 repetitions; 15 s' hold; 3 sets Repetition increases progressively
*Myofascial Release Approach (MFR)*		
Deep stripping [18]	Plantar fascia → Calcaneus Calf muscles Deep posterior leg compartment	Each 5–7 repetitions; 15–30 s' hold; 1–3 sets Application of gentle‐firm‐deep pressure
*Conventional Physiotherapy for Both Groups*		
Ankle strengthening exercise [19, 22]	Resistance exercise (dorsiflexion and plantarflexion with resistance band); towel crunch; heel raise	10 reps; 10 s hold; 1–3 sets
Therapeutic ultrasound [20]	Application of therapeutic pulse ultrasound	Intensity of 1.8 W/cm^2^ and frequency of 1 MHz; 5 min
Ice compression [21]	To reduce pain and prevent inflammation Use an ice cube and an ice pack	8 min

*Note:* Applicable for every exercise: 15 s of rest between each set, and 1 min of rest between different modes of exercise.

The duration and frequency of sessions may be adjusted individually based on each participant's condition. To ensure accurate tracking, a monitoring sheet is maintaining for each participant attending every session.

### Outcome Measurements

2.7

Baseline sociodemographic and clinical characteristics were collected immediately after obtaining informed consent from participants and before the initiation of the intervention. All primary and secondary outcomes were planned to analyze at three time points: baseline (Week 0), posttest (Week 8), and follow‐up (Week 20), by four trained and blinded assessors.

### Sociodemographic and Clinical Characteristics

2.8

The researcher developed a structured questionnaire to collect sociodemographic and clinical characteristics from participants. This includes personal details such as age, gender, and occupation; demographic information; and condition‐related variables such as BMI, type and duration of DM, radiological confirmation of diagnosis, duration of PHP, affected foot, type of footwear, and duration of footwear use.

### Primary Outcome

2.9

#### Pain Intensity

2.9.1

Pain intensity was measured using a 10 cm Visual Analog Scale (VAS), a widely accepted tool for evaluating pain. The scale consists of a 10 cm horizontal line anchored at 0 (“no pain”) and 10 (“severe pain”). The VAS demonstrates excellent test–retest reliability (ICC = 0.99; 95% CI: 0.989–0.992) and strong validity [23].

### Secondary Outcomes

2.10

#### Range of Motion (ROM)

2.10.1

Participants actively perform dorsiflexion and plantarflexion using a digital dynamometer (ActiveForce‐2), with measurements recorded in degrees via the device's app. A study reported excellent reliability for the portable dynamometer, with ICC values of 0.972 for dorsiflexion and plantarflexion. Additionally, strong reliability was found between right and left ankle measurements: plantarflexion ICC = 0.89 and dorsiflexion ICC = 0.94 [24, 25].

#### Muscle Strength

2.10.2

A portable digital hand dynamometer (ActiveForce‐2) and its companion app is used to assess isometric strength of the dorsiflexors and plantarflexors of the affected foot, with measurements recorded in kilogram‐force (kgf). Previous research has demonstrated that portable dynamometers exhibit high inter‐rater and test–retest reliability, with strong correlations for dorsiflexion and plantarflexion strength (*r* = 0.827, *r* = 0.973) [25].

#### Disability and Activity Limitation

2.10.3

The Foot Function Index (FFI) is used to evaluate overall pain, disability, and activity limitation. This self‐administered questionnaire comprises 23 items across 3 subscales: pain (9 items), disability/function (9 items), and activity limitation (5 items). Previous studies have reported test–retest reliability ranging from 0.69 to 0.87 and internal consistency between 0.73 and 0.96, alongside strong correlations with clinical measures of foot pathology, confirming its validity as a standard assessment tool. FFI scores were planned to analyze at both the total and subscale levels, with measurements taken at baseline, postintervention, and follow‐up. Between‐group and within‐group comparisons will be performed for each subscale to provide a domain‐specific interpretation of treatment effects [26, 27].

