## Abstract

**Background and Aims:**

Plantar heel pain (PHP) is prevalent among individuals with diabetes mellitus and contributes to chronic pain, reduced mobility, muscle weakness, and activity limitation. Conventional treatments such as medications and physical modalities are used but often lack long‐term effectiveness and cost‐efficiency. Physiotherapy approaches, including Structural Diagnosis and Management (SDM) and Myofascial Release (MFR), have demonstrated benefits; however, comparative evidence in diabetic populations is limited. This study aimed to evaluate and compare the effectiveness of SDM and MFR in reducing pain and disability and improving function in people with diabetes mellitus experiencing PHP.

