In physiotherapy practice, various interventions have been reported, including electrical modalities such as iontophoresis with dexamethasone 0.4% or acetic acid 5%, which give pain relief and improve function within 2–4 weeks. Manual therapy techniques such as nerve mobilization (effective within 1–3 months), soft tissue mobilization, passive neural mobilization, gliding of the ankle joint posteriorly, the subtalar joint laterally, and the first tarsometatarsal joint anterior‐posteriorly, and distraction manipulation of the subtalar joint are also commonly used to reduce pain and restore mobility for people with PHP [13]. Other conservative approaches include taping, orthotic devices, and night splints. Calcaneal taping may provide pain relief temporarily within 7–10 days. Orthotic devices, such as specially designed foot orthoses, reduce pain and improve function over a short‐term period of approximately 3 months. Night splints, available in sock‐type, anterior, or posterior designs, are recommended for individuals with PHP lasting 6 months or more. They are typically worn for 1–3 months [15].

Studies on PHP in nondiabetic patients have revealed that Myofascial Release (MFR) to the calf muscles and plantar fascia is a practical manual therapy technique [16]. Recent studies indicate that the Structural Diagnosis and Management (SDM) approach—targeting calf muscles, plantar fascia, lower limb muscles, and myoneural structures—offers short‐ to intermediate‐term pain relief and improved functional independence in people with PHP. However, PHP is higher in DM cases and has a poor prognosis, and there is a significant research gap addressing effective manual therapy approaches for PHP in people with DM [17, 18, 19, 20, 21].

Therefore, the primary goal of this study is to compare the effectiveness of two manual therapy approaches, SDM and MFR, in treating individuals with PHP who have DM. The objectives are (1) to determine baseline compatibility of both groups in sociodemographic and clinical variables; (2) to measure between‐group and within‐group posttreatment outcomes in pain, ankle ROM, muscle strength, activity limitation, and disability; and (3) to compare the follow‐up outcomes of both groups. After 8 weeks of interventions, the SDM or MFR group is expected to show better improvement in PHP for people with DM.

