### Randomization and Blinding

2.5

Eligible participants with written informed consent were randomly allocated to their respective groups, either the SDM or the MFR group. The randomization sequencing process was conducted using the “Rand” function in Microsoft Excel 2013 software. A sequential list of participants' IDs, sorted according to the randomly generated numbers. This procedure helps to prevent bias. Participants were allocated to a parallel intervention group in a 1:1 ratio. This is an assessor‐ and participant‐blinded randomized clinical trial, with outcome assessors and participants blinded to group allocation. Physiotherapists delivering manual therapy could not be blinded, but both groups received identical conventional physiotherapy to control for nonspecific effects. Therapists were trained to follow standardized protocols and avoid discussing treatment or outcomes with participants or assessors to minimize bias. Inter‐rater reliability for manual techniques will be established, and any unblinding will be documented and reported.

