### Data Analysis

2.15

Data analysis will be performed by an independent statistician using SPSS version 22, with anonymized and encrypted data to ensure confidentiality. Prior to analysis, data will be screened for completeness and outliers. The parametricity of the data will be assessed using the Kolmogorov–Smirnov and Shapiro–Wilk tests, supported by evaluation of skewness and kurtosis and visual inspection of data distribution through histograms and normal probability plots. Descriptive statistics, including mean and standard deviation for normally distributed variables, median and interquartile range for non‐normally distributed variables, and frequency and percentage for categorical variables, will be used to summarize continuous and categorical data. Baseline characteristics, including body mass index and duration of diabetes, will be reported to assess group comparability, and exploratory subgroup analyses for high‐risk participants will be considered if clinically relevant patterns are observed. For comparisons across three time points (baseline, postintervention, and follow‐up), repeated‐measures ANOVA will be applied for normally distributed data, with the Friedman test used as the nonparametric alternative. Between‐group and within‐group differences will be analyzed using independent and paired *t*‐tests for parametric data, or Mann–Whitney *U* and Wilcoxon signed‐rank tests for nonparametric data, as appropriate. The laterality of PHP (unilateral or bilateral) will be recorded and incorporated into the analysis to minimize potential confounding effects on ROM and muscle strength outcomes. Effect estimates and mean differences will be reported with 95% confidence intervals alongside *p* values. All statistical tests will be two‐tailed, with statistical significance set at *p* < 0.05, *p* < 0.01, and *p* < 0.001. In addition, baseline, posttest, and follow‐up change scores will be evaluated, and an intention‐to‐treat analysis using the last observation carried forward method will be applied to handle missing data and preserve the validity of the analysis.

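### Within-arm before-after tests are given a role in interpreting treatment effects, although both arms are active and share co-treatment, so only the between-group contrast can carry that inference

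*Protocol article*

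**What the plan says.** Section 2.10.3 (Disability and Activity Limitation) states that between-group and within-"group comparisons will be performed for each subscale to provide a domain‐specific interpretation of treatment effects". The valid randomized comparison is named first, but the within-group comparison is given the same purpose in the same sentence.

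Two other places plan within-group testing more widely. Objective 2 in the Introduction covers between-group and within-group results, the latter being "group posttreatment outcomes in pain, ankle ROM, muscle strength, activity limitation, and disability". Section 2.15 (Data Analysis) says that between-group and within-"group differences will be analyzed using independent and paired *t*‐tests for parametric data", with Mann–Whitney and Wilcoxon signed-rank tests as the non-parametric versions. All tests are two-tailed with significance thresholds, and no sentence restricts the within-group results to description.

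On design, section 2.1 describes two arms, SDM and MFR, allocated 1:1. Section 2.6 says: "Both groups receive designed conventional physiotherapy treatment including ankle strengthening exercise, therapeutic ultrasound, and ice compressions". Section 2.5 gives the reason: "both groups received identical conventional physiotherapy to control for nonspecific effects". The abstract words the aim as follows: "This study aimed to evaluate and compare the effectiveness of SDM and MFR in reducing pain and disability".

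**The concern.** A before-after change in one arm is the sum of several things: the natural course of heel pain over 8 or 20 weeks, regression to the mean in people enrolled while in pain, the shared conventional physiotherapy, and the manual technique. With no arm that receives conventional physiotherapy alone, nothing in the trial separates the last of these from the rest. Section 2.5 says the co-treatment is identical in order to control for non-specific effects. That control works only when one arm is subtracted from the other. A paired test within an arm brings those effects back.

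Two unsupported conclusions then become possible. If both paired tests are significant, the report may say that both techniques work. If one is significant and the other is not, it may say that one works and the other does not, even where the direct comparison shows no difference. The randomized design supports neither statement.

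**Working it through.** The plan gives no figure for within-arm change, so there is none of its own to reproduce here. The calculation illustrates how often within-arm tests would be significant when the two therapies do not differ at all.

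**Inputs**
- 45 per arm (section 2.2); two-sided tests at 0.05 (section 2.15).
- Shared improvement d, in SDs of the change score: not in the documents. Assumed 0.3, 0.5 and 0.8.
- Identical therapies, so any change is common to both arms.

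**Step 1. One arm.** The paired t-test has 44 degrees of freedom and non-centrality d × √45, which is 2.01, 3.35 and 5.37. Its power p is 0.503, 0.907 and 0.9995.

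**Step 2. Two independent arms.** Both arms significant: p². Exactly one significant: 2p(1 − p).

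| Shared improvement | One arm, p | Both arms, p² | Exactly one, 2p(1 − p) |
|---|---|---|---|
| 0.3 SD | 0.503 | 0.253 | 0.500 |
| 0.5 SD | 0.907 | 0.822 | 0.169 |
| 0.8 SD | 0.9995 | 0.999 | 0.001 |

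With no shared improvement, p = 0.05 and both arms are significant in 0.05² = 0.0025 of trials. The function 2p(1 − p) cannot exceed 0.50, so the 0.3 SD row shows its maximum.

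**Step 3. Between-group test.** In simulations of 20,000 trials per scenario, the between-group t-test on change scores was significant in 4.9% to 5.1% of trials whatever the shared improvement. The shared part cancels.

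**Step 4. Sensitivity to pre-post correlation.** If the improvement D is instead expressed in SDs of the score itself, d = D/√(2(1 − r)), which equals D at r = 0.5. For r from 0.3 to 0.7 (assumed):
- D = 0.3: p runs from 0.384 to 0.719, and both arms are significant in 15% to 52% of trials.
- D = 0.5: p runs from 0.792 to 0.989, and both arms are significant in 63% to 98%.
- D = 0.8: p runs from 0.993 to 1.000, and both arms are significant in 99% to 100%.

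**Step 5. Fewer patients.** With 36 per arm (half of the 72 that section 2.2 requires before dropout), p is 0.417, 0.831 and 0.997, and both arms are significant in 17%, 69% and 99% of trials.

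**The case against.** The strongest reply is that the trial is mainly comparative. The Introduction gives the primary goal as a comparison of the two approaches, the abstract's results and conclusions speak of a comparison, and section 2.15 already plans between-group tests and mean differences with 95% confidence intervals. Adding paired tests biases none of those estimates. No sentence announces a conclusion that both therapies are effective, or a comparison of one arm's p value with the other's. All this stands, and it limits the point to interpretation. It does not remove it, because section 2.10.3 itself assigns within-group comparisons to the reading of treatment effects.

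Four stronger readings are tempting and are not supported:
- A reader might infer that every within-group test is declared a treatment effect. That wording covers only the Foot Function Index subscales. For pain, range of motion and strength, the paired tests are planned without that label, though also without any limit to description.
- A reader might infer that both therapies will look effective whatever they do. This holds only if patients in both arms improve for shared reasons. The documents give no size for this, and section 2.4 sets no minimum pain score from which regression to the mean could be gauged. At 0.3 SD, both arms are significant in only about a quarter of trials.
- A reader might infer that the investigators expect no difference and rely on the within-group tests. The Introduction says the opposite: one group is expected to improve more.
- A reader might take the one-in-two chance of discordant arms as typical. It is the maximum, and falls to about 17% at 0.5 SD and 0.1% at 0.8 SD.

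**Conclusion.** The point holds as a fault of interpretation written into the plan. Section 2.10.3 gives within-group comparisons a share in interpreting treatment effects, and objective 2 and section 2.15 plan such tests for all outcomes without confining them to description. With two active arms and identical co-treatment, no within-arm change can be attributed to SDM or to MFR. Following the stated rule would therefore give a conclusion the design cannot support.

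How often this would mislead depends on a shared improvement that the documents do not give. Across the assumed 0.3 to 0.8 SD, two identical therapies would both appear to work in about 25% to over 99% of trials. The argument against the inference itself needs none of these assumptions. The between-group analysis is unaffected, so the point should be corrected before analysis but does not threaten the trial's main comparison.

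**What to change.** - In sections 2.10.3 and 2.15, state that treatment effects, for every outcome and subscale, are judged only by the between-group difference with its 95% confidence interval.
- Report within-arm changes descriptively, as mean change with a confidence interval and no p value, in place of the paired and Wilcoxon tests.
- Reword objective 2 to match, and change the abstract's aim from evaluating and comparing to comparing.

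This is a change of wording with fewer tests. It needs no new data, and section 4 reports that the trial is still recruiting, so it can be made before analysis. The price is that the report can no longer state that either arm improved significantly.

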### Study Procedure

2.11

After screening by trained research assistants, eligible participants were thoroughly informed about the study's objectives and procedures, and then obtain their written informed consent. Once screened, participants were randomly assigned to their allocated groups using a predetermined randomization sequence to ensure unbiased allocation. Four blinded assessors collected baseline data at the study centre using an ethically approved questionnaire designed specifically for this research, which includes sociodemographic information and clinically relevant measures to confirm baseline compatibility with no statistically significant differences between groups. Following the baseline assessment, participants receive their assigned intervention for 8 weeks. After this period, blinded assessors will perform posttest (Week 8) and follow‐up (Week 20) evaluations by measuring primary and secondary outcome variables. This entire study procedure strictly following the SPIRIT 2013 guidelines (Table 1), ensuring methodological rigor and ethical compliance throughout the study.

### Safety Measures and Adverse Reaction Management

2.12

Although no adverse events are anticipated from the treatment, the monitoring team remains vigilant and promptly notifies the appropriate healthcare professionals of any unexpected occurrences that may arise during or after the intervention. All treatment procedures are thoroughly documenting in daily SOAP notes to ensure clear records and to prevent any future misunderstandings or complaints from participants. Before initiating the intervention, the physiotherapist carefully screens for any contraindications. If participants experience any discomfort, pain, or skin irritation after the treatment, they should immediately report these symptoms to both the physician and physiotherapist. Identified any harmful effects, which will be transparently reported by the researcher in the final publication. Additionally, an adverse event reporting checklist is used throughout the intervention period to facilitate systematic monitoring.

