Systematic review between (1994 and 2013) reports, 4.5%–35.0% of Bangladeshi people have DM. The number might rise to 13.7 million by 2045 [10]. Approximately one million individuals with DM visit physicians for PHP [11]. Globally, 0.85% of diabetic people have PHP; among them, 1.31% have type‐2 and 0.92% have type‐1 DM [12]. The clinical presentation and biomechanical factors of PHP are similar in both nondiabetic and diabetic patients. However, in DM cases with PHP, elderly women with a high BMI are the most vulnerable group. In DM cases, degeneration of the plantar fascia and repetitive micro‐tears cause relapsing inflammation and delayed healing, creating a vicious cycle of injury and pain.

Shortening of the calf muscle leads to a series of biomechanical abnormalities, such as a decrease in the range of motion (ROM) of dorsiflexion and an increase in stress to the perifascial structures. Diagnosis of PHP can be made based on plantar fascia, heel spur, or myofascial abnormalities of the foot, according to the International Statistical Classification of Diseases and Related Health Problems (ICD) category. Clinical features are categorized according to specific diagnosis. Some clinical examination, such as the windlass test, longitudinal arch angle, tarsal tunnel syndrome test, and active and passive dorsiflexion ROM in the ankle joint, supports the diagnosis [13, 14].

Intervention guidelines for PHP in nondiabetic and diabetic patients are reported similarly in the previous clinical practice guidelines. Medications include anti‐inflammatory agents, such as NSAIDs. Many studies reported the significance of steroid injections in PHP in nondiabetic patients and some in diabetic patients to reduce inflammation, improve pain, and functional conditions. However, steroids have a long‐term consequence of tendon and osseous degeneration [13].

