### Study Design

2.1

This study was a multicenter, parallel, assessor‐ and participant‐blinded randomized clinical trial with an 8‐week intervention period, conducted at the Nurul Islam Diabetic Centre, Ibn Sina Diabetes Centre, and City Hospital & Diabetic Care, Jashore, Bangladesh, from September 2025 to March 2026. Eligible participants were randomly assigned in a 1:1 ratio to either the SDM or MFR group. This trial has been designed following the Standard Protocol Items: Recommendations for Interventional Trials (SPIRIT) guidelines, which offer a comprehensive framework for developing RCT protocols, as detailed in Table 1. Additionally, the Consolidated Standards of Reporting Trials (CONSORT) statement has been adopted to improve the quality and completeness of RCT reporting, as shown in Figure 1.

**Table 1 hsr272255-tbl-0001:** SPIRIT table.

Timepoint	Enrollment	Allocation		Post‐allocation	
	−*T* _1_	*T* _0_	*T* _1_	*T* _2_	*T* _3_
*Enrollment*					
Eligibility screening	X				
Informed consent		X			
Demographic and clinical assessment			X		
Group allocation		X			
*Intervention*					
SDM Group			X	X	
MFR Group			X	X	
*Assessment*					
Pain intensity			X	X	X
Range of motion			X	X	X
Muscle strength			X	X	X
Foot Function Index			X	X	X

*Note:* −*T*
_1_, prestudy enrolment; *T*
_0_: group allocation; *T*
_1_, baseline before intervention; *T*
_2_, measurement after 8 weeks; *T*
_3_, measurement after 20 weeks.

Abbreviations: MFR, myofascial release; SDM, Structural Diagnosis and Management.

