## Discussion

3

The primary aim of this study is to evaluate the effectiveness of the SDM Approach versus MFR in treating PHP in diabetic patients. Previous research indicates that approximately one million individuals are referred annually to a doctor for a definitive diagnosis of plantar fasciitis. A recent cohort study identified the prevalence of plantar fasciitis as 720,000, with an incidence of 0.85% among diabetic patients [8, 9, 10, 11, 12]. Several studies have explored various interventions that could provide interim relief from PHP, plantar fasciitis, and heel spurs, such as considering and providing anti‐inflammatory agents, electrical modalities, and manual therapies like nerve mobilization, often focusing solely on the central pain area rather than the affected structures [14, 15].

However, our study considers the potential scope by including the associated structures, which may be a more critical factor in achieving sustainable outcomes. Without addressing these, diabetic patients are increasingly at risk of this foot condition, which often remains untreatable and misunderstood. To date, no research has directly compared and analyzed yet the effectiveness of SDM versus MFR in treating PHP in people with diabetes mellitus. The long‐term objective of this study is to play a vital role in the management of this global condition.

This study offers several significant benefits. It marks the first attempt in Bangladesh to compare the effectiveness of SDM and MFR in managing PHP among individuals with diabetes mellitus, incorporating a 12‐week follow‐up period. The study highlights the potential contribution of these intervention strategies not only in reducing pain but also in improving functional outcomes that enhance patients' quality of life. By addressing a significant gap in existing research, this study may offer valuable insights for clinical practice and future research in DF management.

However, limitations include the focus on a specific area in Bangladesh, which may restrict the broader applicability of its findings. Additionally, the presence of multiple comorbidities and a limited sample size are notable constraints. Future research should involve a larger and more diverse population, with an extended follow‐up duration. It is also recommended that subsequent studies adopt more rigorous research designs, suited to resource‐limited settings, to enhance the validity and generalizability of the findings.

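### The only harms tool called systematic is tied to the 8-week intervention period, so harms in Weeks 8–20 rest on unsolicited reporting and may be under-counted

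*Protocol article*

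**What the plan says.** Section 2.12 of the protocol article (Safety Measures and Adverse Reaction Management) describes several routes for harms. The one it calls systematic is the checklist: "an adverse event reporting checklist is used throughout the intervention period to facilitate systematic monitoring". Earlier in the same section the monitoring team "promptly notifies the appropriate healthcare professionals of any unexpected occurrences that may arise during or after the intervention". Participants are also told to report symptoms that follow treatment, and harms that are identified are to be published. Section 2.14 adds two independent monitors whose remit includes adverse effects. None of these other routes has an end date.

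Section 2.6 fixes the length of treatment: "Both groups undergo an 8‐week intervention program, consisting of three sessions per week". Section 2.1 uses the same 8 weeks for the intervention period, and the note to Table 1 defines the last time point as "measurement after 20 weeks". Section 2.11 says what happens at the later visits: "blinded assessors will perform posttest (Week 8) and follow‐up (Week 20) evaluations by measuring primary and secondary outcome variables". Table 1 lists pain, range of motion, strength and the Foot Function Index at the last time point, and has no row for adverse events.

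**The concern.** The stated purpose and the stated tool do not match. Section 2.12 sets a scope for harms that extends beyond treatment, then ties its systematic instrument to the treatment weeks. The trial brings participants back at Week 20 to see whether effects last, so outcomes are collected on a fixed schedule for 20 weeks and adverse events by checklist for 8.

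What is at stake is the completeness of the harms data. The article commits to open reporting of harmful effects, but that commitment can cover only what has been identified. Harms asked about with a form and harms that participants must volunteer are not found equally often. A final table mixing the two would be hard to read as a 20-week harms record.

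**Working it through.** **Inputs, all from the protocol article**

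- Checklist window: the intervention period (section 2.12).
- Length of that period: 8 weeks (sections 2.1 and 2.6).
- Last assessment: Week 20 (Table 1, sections 2.7 and 2.11).
- Follow-up as described in the Discussion: "incorporating a 12‐week follow‐up period".

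**Step 1. Reproduce the article's own figure.** Week 20 − Week 8 = 12 weeks, which agrees with the Discussion.

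**Step 2. Coverage of the checklist as written.** 8/20 = 40% of the observation period is covered and 12/20 = 60% is not. With the checklist also completed up to and at Week 20, coverage is 20/20 = 100%.

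**Step 3. Do the other routes fill the 12 weeks?**

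- The daily treatment notes document treatment procedures, so they go with the sessions.
- Self-report is open-ended, but depends on the participant coming forward. No study visit is listed between Week 8 and Week 20.
- The two monitors have no Week 8 limit, but no schedule of active collection is given for them.
- The Week 20 visit is described through the outcome measures alone.

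The gap therefore lies in solicited collection. Reporting as such is not cut off at Week 8.

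**Step 4. Can an under-count be sized?** Two quantities are needed that the documents do not give, so both are assumptions here: r, the weekly harm rate after treatment relative to the rate during treatment, and c, the share of later harms captured without a form. Capture during Weeks 0–8 is taken as complete.

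- Share of all harms arising in Weeks 8–20 = 12r / (8 + 12r)
- Share of all harms missed = that share × (1 − c)

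| r (assumed) | Share arising in Weeks 8–20 | Missed, c = 0 | Missed, c = 0.5 | Missed, c = 0.9 | Missed, c = 1 |
|---|---|---|---|---|---|
| 0.1 | 1.2/9.2 = 13% | 13% | 6.5% | 1.3% | 0% |
| 0.25 | 3/11 = 27.3% | 27.3% | 13.6% | 2.7% | 0% |
| 0.5 | 6/14 = 42.9% | 42.9% | 21.4% | 4.3% | 0% |
| 1.0 | 12/20 = 60% | 60% | 30% | 6% | 0% |

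The result runs from 0% to 60% depending only on the assumptions. The table shows that the answer is open; it is not an estimate.

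**The case against.** The strongest reply is that section 2.12 is coherent as it stands. The checklist is introduced as an addition to vigilance that has no end date, and closer surveillance during treatment with lighter surveillance afterwards is a reasonable design. The phrases about events after the intervention or after treatment could mean after a session rather than after Week 8. Nothing in the text says that adverse-event collection ends at Week 8. Worsened pain, lost motion, weakness or disability at Week 20 would also show in the outcome measures. Finally, this is a journal article, and a fuller protocol may set out the harms window.

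Much of this stands. Collection is not stated to stop, so the claim must be limited to solicited collection. The reading of after the intervention as after a session is possible, although the article generally uses the word for the whole 8-week course; section 2.11, for example, has participants receive it for 8 weeks. The outcome measures do overlap with some harms, but they are not adverse-event records and do not replace a checklist. The point about condensed articles carries less weight, because the checklist window is stated here rather than left out, and it is shorter than the scope stated beside it.

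Two stronger readings are tempting and not supported:

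- A reader might infer that participants who stop treatment early drop out of the checklist. Section 2.1 defines the 8-week period for the trial, and nothing makes checklist use depend on attendance.
- A reader might take the Introduction, which says that micro-tears and degeneration of the fascia in diabetes "cause relapsing inflammation and delayed healing, creating a vicious cycle of injury and pain", as evidence of delayed harm from manual therapy. That sentence describes the disease and says nothing about treatment.

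**Conclusion.** The point holds as a limit on harms ascertainment. Followed as written, the article schedules no solicited collection of adverse events for 12 of 20 weeks (60%), while its own safety section reaches beyond the intervention. Harms in that period rest on unsolicited reporting and on monitoring without a stated schedule, and may be under-counted. This assumes that the intervention period means the 8 weeks of section 2.1 and that the full protocol adds no later checklist.

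The size of any under-count cannot be derived. With 90 participants and no dropout, 90 × 12 = 1,080 person-weeks fall outside the checklist. A reader might take that figure as an amount of missed harm, but it is only observation time. Nor do the documents support a bias between arms, since both follow the same schedule. The primary pain comparison is unaffected. The change is worth making because it is cheap and because, with recruitment described as continuing (section 4), it could still be made.

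**What to change.** Replace the checklist sentence in section 2.12 with wording such as: the adverse-event checklist is used from first treatment through the Week 20 visit for every randomised participant, and is completed with the same questions in both arms at the Week 8 and Week 20 visits, after the blinded outcome measures. Add an adverse-event row to Table 1 to match, and state that harms will be reported by arm for Weeks 0–8 and Weeks 8–20.

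The order within the visit matters: answers about reactions to treatment could reveal the arm, so the form should come after the assessor has finished the outcome measures.

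The cost is one changed sentence, one table row and a few minutes at two visits that already exist, with no new visit or staff. More minor events will be recorded, and the final report should say that this reflects asking.
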